Minimal residual disease (MRD) is defined as the presence of tumor cells in the blood, bone marrow or lymph nodes not detected by conventional staging procedures [14]. Patients who have MRD after surgery are not completely cured and therefore at high risk of developing disease recurrence. Development of a highly specific and sensitive (bio)marker test indicative for MRD would allow identification of the subset of patients likely to experience recurrence of disease, thereby improving the selection of patients who may benefit from adjuvant treatment. In adjuvant trials, this would solve problems of high numbers needed for inclusion and dilution of effectiveness of adjuvant treatment by inclusion of many already cured participants [15].

Cell-free circulating tumor DNA (ctDNA) has a strong potential for being this sensitive, and yet specific biomarker. ctDNA consists of small fragments (usually 150–200 bp) of tumor-derived DNA containing tumor-specific mutations which can be detected in liquid biopsies such as blood samples [16–18]. Because of the short half-life of ctDNA (estimates ranging from 15 to 120 min) the presence of ctDNA in blood samples taken several days after surgery presumably reflects a state of MRD [19–21]. Patients with MRD have the highest risk for disease recurrence.

Recently, the presence of ctDNA after tumor resection demonstrated a very strong prognostic value for disease recurrence in stage II CC, with a 2-years RR of 79.0% versus 9.8% in patients with and without detectable ctDNA after surgery respectively [21]. In this study the univariate prognostic value of ctDNA was much higher than that of pT4 status (hazard ratio of 14 versus 2.6, respectively). There are several ongoing trials that use ctDNA in prognostication (NCT03637686, NCT03737539, NCT03416478, NCT03312374, NCT02842203, NCT03615170) and treatment (NCT03748680, ACTRN12615000381583, NRG-GI 005) of non-metastatic CC, but to date there are no results available of randomized controlled trials (RCTs) that use ctDNA for selection of ACT treatment.

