### Randomization

About 1 week after surgery, when the histopathological report is finished, MEDOCC patients who are eligible for MEDOCC-CrEATE will be randomized 1:1 to the intervention or control arm using SLIM, an online platform to manage patient inclusion including a randomization service. The computer generated randomization schedule is stratified by T-stage and uses permuted blocks of random sizes. Allocation concealment will be ensured, as the service will not release the randomization code. Only patients randomized to the intervention arm will be informed about MEDOCC-CrEATE according to the TwiCs design [22].

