### Secondary endpoints

The most important secondary endpoint is 2-year RR in patients with detectable ctDNA in their blood, expressed as the proportion of patients that experience a recurrence within 2 years after surgery. Detection of recurrences (in months after surgery) will occur by standard follow-up investigations including 3–6 monthly blood sampling of tumor marker CEA and 6 monthly imaging with ultrasound liver or CT abdomen and when indicated by symptoms. Radiological and/or histopathological evidence is used to confirm the recurrence; the date of the said investigation is considered the date of recurrence.

Data about follow-up, recurrences and survival are routinely collected within PLCRC using the Netherlands Cancer Registry (NCR), managed by the Netherlands Comprehensive Cancer Organisation (IKNL) to provide insight in the characteristics and magnitude of cancer in the Netherlands [28].

Other secondary endpoints include 2-year RR in a per-protocol analysis, 5-year RR (intention-to-treat and per-protocol analysis), time to recurrence (TTR), 2- and 5-year disease free survival (DFS) rate, 5- and 7-year disease-related OS rate, 2- and 5-year RR in patients with undetectable ctDNA after surgery, quality of life (QoL) and cost-effectiveness of the ctDNA-guided strategy.

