### Sample size considerations

The primary endpoint is the proportion of ctDNA positive patients starting with ACT. However, 2-year RR in the ctDNA positive patients after surgery is an important secondary endpoint and the power calculation is performed for this secondary endpoint. We estimate that, similar to effectiveness in stage III CC patients, ACT in ctDNA-based high-risk stage II CC patients will lead to a 30% absolute reduction of recurrences within 2 years after surgery. In the observational trial 79% of patients with detectable ctDNA experienced disease recurrence within 2 years after resection [21].

With a power of 80% and an alpha of 0.05, 30 patients with detectable ctDNA need to be included in both arms. Assuming a prevalence of ctDNA after surgery of 5%, and adjustment for loss to follow-up and rejection of adjuvant therapy in the intervention arm of 10%, a total sample size of 1320 patients is calculated (660 in each arm). We expect few patients with detectable ctDNA in the intervention group to refuse ACT, because patients are selected upfront for being in a physical condition to receive ACT and the established prognostic value of detectable ctDNA is high.

We assume that cross-over from the control arm to the intervention arm will not occur, because only eligible patients randomly selected in the cohort and allocated to the intervention arm will be informed about the trial and have the opportunity for immediate analysis of ctDNA. Patients in the control group will not be informed about the trial or their ctDNA status.

We assume that 90% of patients in the intervention arm with detectable ctDNA will be treated with ACT. The proportion of patients starting with chemotherapy, the primary endpoint, can in that instance be determined with a margin of error (width of the 95% confidence interval) of 11%.

We expect to complete recruitment of patients within 2–3 years with more than 20 participating Dutch hospitals.

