### Data analysis

Data will be analyzed according to the intention-to-treat principle for the primary endpoint and the secondary endpoint of 2-year RR in patients with detectable ctDNA after surgery. In this analysis we expect to compare 30 patients with detectable ctDNA who received ACT in the intervention arm with 30 patients with detectable ctDNA in the control arm, i.e. based on ctDNA analysis performed retrospectively, at least 3 months after surgery, and not disclosed to patients and treating physicians. The proportion of patients that experience a recurrence in both arms will be compared by means of a chi-square test. In addition, for other secondary endpoints and exploratory analyses we will analyze time-to-event outcomes in patients in both arms with detectable ctDNA after surgery. Differences in time-to-event outcomes will be analyzed by standard survival methods, e.g. Kaplan-Meier curves compared by log-rank tests. Cox’s proportional hazards models will be used for multivariable analysis.

Comparison of QoL of the ctDNA positive patients in both study arms will be done using repeated measurements methods and including ACT as factor. QoL will also be analyzed for the whole population in both arms of the study. Treatment differences at each QoL assessment time point will be compared by means of the Wilcoxon Rank Sum Test.

A lifetime horizon will be applied for the cost-effectiveness analysis, parametric survival functions will be used to extrapolate DFS and OS curves beyond 5 years.

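### The powered 2-year recurrence comparison is an unstratified chi-square test on crude proportions, although randomisation is stratified by T-stage and T-stage balance is not ensured among the roughly 60 ctDNA-positive patients compared

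*Protocol article*

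**What the plan says.** The Secondary endpoints section makes 2-year recurrence in patients with detectable ctDNA the leading secondary endpoint, "expressed as the proportion of patients that experience a recurrence within 2 years after surgery". The Sample size considerations section bases the power calculation on it: "With a power of 80% and an alpha of 0.05, 30 patients with detectable ctDNA need to be included in both arms". Data analysis fixes the test: "The proportion of patients that experience a recurrence in both arms will be compared by means of a chi-square test".

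Three other statements bear on that choice.

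- Randomization: "The computer generated randomization schedule is stratified by T-stage". Patient selection and recruitment explains that pT4 status is the stratification factor because some pT4 patients are not offered adjuvant chemotherapy (ACT).
- Background gives the univariate prognostic strength of ctDNA and of pT4 as "hazard ratio of 14 versus 2.6".
- Sample size considerations enlarges the trial by a combined 10% for refusal of ACT and "adjustment for loss to follow-up".

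For time-to-event outcomes, including time to recurrence, the article has censoring rules and plans Kaplan-Meier, log-rank and multivariable Cox analyses. No strata are named there either.

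**The concern.** A factor judged important enough to stratify the randomisation would normally enter the main analysis. It matters more than usual here, because the comparison is confined to a subset of about 5% that is identified after randomisation. The blocks balance T-stage over the whole trial and leave its distribution among ctDNA-positive patients to chance. With about 30 per arm, a few pT4 patients more on one side move the crude recurrence proportion.

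A crude 2-year proportion also needs a known status at 2 years for everyone. A patient lost at 14 months without recurrence must be either dropped or counted as recurrence-free. Neither choice uses the information correctly.

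The Discussion says that a significant and substantial difference in recurrence should lead to implementation in practice. The comparison behind that conclusion should not be open to the challenge that the arms differed by chance in a known prognostic factor.

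**Working it through.** **1. The plan's own figure.** Inputs from Sample size considerations: "79% of patients with detectable ctDNA experienced disease recurrence within 2 years after resection", and ACT "will lead to a 30% absolute reduction of recurrences within 2 years after surgery". So p1 = 0.79, p2 = 0.49 and the pooled proportion is 0.64. The formula is n = [z_a √(2 × 0.64 × 0.36) + z_b √(0.79 × 0.21 + 0.49 × 0.51)]² / 0.30².

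- One-sided 0.05: (1.645 × 0.679 + 0.842 × 0.645)² / 0.09 = 30.6, close to the stated 30.
- Two-sided 0.05: (1.960 × 0.679 + 0.842 × 0.645)² / 0.09 = 39.0.

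The stated 30 therefore reproduces only one-sided. Everything below is two-sided. Chi-square power at 30 per arm is 68.6%, by formula and exactly. The planned 660 per arm (30 / 0.05 × 1.1) at 5% prevalence gives 33 ctDNA-positive patients per arm, where exact power is 75.0%.

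**2. How often the arms differ in pT4.** The pT4 share among ctDNA-positive patients is not in the article; 10%, 20% and 30% are assumed. The pT4 counts in the two arms are treated as independent Binomial(n, share), and P(|X1 − X2| ≥ 0.1n) is computed.

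| Per arm | Difference needed | 10% pT4 | 20% pT4 | 30% pT4 |
|---|---|---|---|---|
| 30 | 3 patients | 27% | 42% | 48% |
| 33 | 4 patients | 15% | 28% | 35% |

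**3. What an imbalance does.** Take a 20% share and hazard ratio 2.6, and let H be the cumulative hazard at 2 years in non-pT4 patients. Solving 0.8(1 − e^−H) + 0.2(1 − e^−2.6H) = 0.79 gives control recurrence of 74.5% in non-pT4 and 97.1% in pT4. The same equation set to 0.49 gives 42.2% and 76.0%. An excess of 10 percentage points in pT4 share then shifts the crude rate by 0.1 × 22.7 = 2.3 points (control) or 0.1 × 33.8 = 3.4 points (experimental), against a planned difference of 30.

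**4. Power of a T-stage-stratified test on the same proportions.** Simulation, 20,000 trials per row, two-sided 0.05, 79% versus 49%, no loss:

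| Per arm | pT4 share | pT4 hazard ratio | Chi-square | CMH | Change (points) |
|---|---|---|---|---|---|
| 30 | 10% | 2.6 | 68.5% | 69.6% | +1.1 |
| 30 | 20% | 2.6 | 68.3% | 70.7% | +2.4 |
| 30 | 30% | 2.6 | 68.6% | 72.5% | +3.9 |
| 33 | 10% | 2.6 | 74.7% | 73.8% | −0.9 |
| 33 | 20% | 2.6 | 75.0% | 75.4% | +0.4 |
| 33 | 30% | 2.6 | 74.8% | 76.2% | +1.4 |
| 30 | 20% | 1 | 68.4% | 68.0% | −0.4 |
| 33 | 20% | 1 | 74.8% | 72.9% | −1.9 |

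A repeat with 100,000 trials per row gave the same pattern, and type I error was close to 5% for both tests.

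**5. Loss before 2 years.** With 10% loss at 30 per arm, chi-square power is about 65% if lost patients count as recurrence-free and about 67% if they are excluded. The plan's 10% also covers refusal, so loss alone should be smaller.

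**6. The log-rank alternative.** Stratified log-rank over 2 years, 30 per arm, 20% pT4, hazard ratio 2.6. The rows by month of onset come from 2,500 trials each.

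| ACT effect begins | Chi-square | Stratified log-rank |
|---|---|---|
| at surgery | 68% | 78% |
| after 1 month | 70% | 72% |
| after 2 months | 69% | 69% |
| after 3 months | 70% | 64% |

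A run of 20,000 trials with a 3-month delay gave 68.5% and 62.5%.

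**The case against.** The chi-square test matches the endpoint as defined and the two-proportion effect behind the sample size. Event times and censoring are used elsewhere in the plan, since time to recurrence has its own rules and tests. Registry follow-up should keep loss low. How lost patients are counted, and any covariate adjustment, may be set out in the full protocol or an analysis plan that is not shown. The hazard ratio of 2.6 is a univariate figure for stage II disease, not for ctDNA-positive patients. Only pT4 patients without an ACT recommendation are eligible, so their share may be small.

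Much of this stands. The article's silence on a rule for lost patients is not counted as an error here. What remains is that the article names a specific test, that this test leaves out the stratification factor, and that a crude proportion cannot by construction use partial follow-up.

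A reader might infer three stronger points that the article does not support.

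- **That a T-stage-stratified log-rank test would recover 4 to 10 points of power and should replace the chi-square.** Gains of that order appear only if hazards are proportional from surgery. The Experimental arm section has ACT starting preferably within 8 weeks and at latest 12 weeks after surgery, so a delayed effect is plausible. Step 6 shows the gain disappearing at 2 months and reversing at 3. A log-rank test also compares whole curves rather than the 2-year proportion.
- **That the chi-square is the weakest test available.** Under a 3-month delay it is stronger than the log-rank.
- **That the plan as a whole ignores timing and censoring.** It does not.

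The shortfall of 30 per arm under a two-sided test is a separate matter and adds no weight to this one.

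**Conclusion.** The point holds in a limited form. The powered comparison is unadjusted for the factor that stratified the randomisation, in a subset where balance on that factor is left to chance, and it uses a summary that cannot take in incomplete follow-up.

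The effect on power is small: about +1 to +4 points for CMH at 30 per arm and −1 to +1.5 at 33, with a possible cost of up to about 2 points if pT4 carries no prognostic information in ctDNA-positive patients. These figures rest on an assumed pT4 share of 10-30%, on the hazard ratio of 2.6 carrying over to this subset, and on the plan's 79% versus 49%.

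The case for the change is therefore mainly credibility. The result would be protected against a chance T-stage imbalance of a size that is not rare, and partial follow-up could be used properly. It does not repair the trial's power.

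**What to change.** Keep 2-year recurrence in ctDNA-positive patients as the quantity of interest and amend Data analysis so that the main comparison is stratified by or adjusted for T-stage. Either form would do:

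- a CMH test stratified by pT4 status, with the stratified risk difference and its 95% confidence interval; or
- a T-stage-adjusted difference in 2-year cumulative incidence with its 95% confidence interval, censoring patients at last follow-up and treating death without recurrence as a competing event.

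Only the second uses partial follow-up. If CMH is chosen, state how patients without 2-year status are counted. Fix the stratum weights in advance, because the pT4 stratum will be thin: at 33 per arm, shares of 10-30% give about 3 to 10 patients per arm. Keep the plain chi-square as a sensitivity analysis and leave the log-rank test with time to recurrence.

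The cost is a wording change before the ctDNA-positive arms are compared. T-stage is recorded for randomisation and recurrence dates are already collected, so no new data are needed.

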### Study design

The MEDOCC-CrEATE trial follows the TwiCs design and is performed within the Prospective Dutch ColoRectal Cancer cohort (PLCRC; www.PLCRC.nl) [26]. PLCRC is set up by the Dutch Colorectal Cancer Group (DCCG) and collects clinical data and Patient Reported Outcome Measures (PROMs) at baseline and at multiple time points during follow-up (Fig. 1). At enrollment, patients give informed consent for use of their clinical data and optionally for receiving quality of life questionnaires, collection of biomaterials for research, additional sequential blood sampling and for being approached for future studies conducted within the infrastructure of the cohort, either in accordance with the TwiCs design or not.

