### Patient selection and recruitment

Patients will be recruited in both academic and non-academic hospitals in the Netherlands that are participating in PLCRC. Non-metastatic colorectal cancer (CRC) patients that give informed consent for PLCRC including consent for additional blood sampling at enrollment, will be included in the observational PLCRC substudy MEDOCC (Molecular Early Detection of Colon Cancer) before surgery. The participants are eligible for the current MEDOCC-CrEATE trial if they meet the following criteria after surgery: (1) histopathological confirmed and radically resected stage II CC; (2) age ≥ 18 years; (3) informed consent for PLCRC and MEDOCC including consent for randomization in future trials and use of tissue; (4) physical condition allows treatment with combination chemotherapy consisting of a fluoropyrimidine and oxaliplatin; and (5) no indication for ACT according to the treating physician and/or multidisciplinary board. Patients who are pregnant, have had another malignancy in the previous 5 years, except for carcinoma in situ, or patients with contra-indications for fluoropyrimidines and/or oxaliplatin will be excluded.

Currently the Dutch guidelines recommend ACT for patients with pT4 tumors. However, there is large age- and hospital dependent variation in administration of ACT in this group and in clinical practice not all stage II patients with pT4 tumors will be offered ACT [27]. Therefore, we will include eligible patients with pT4 tumors without a recommendation for ACT according to their treating physician and use pT4 status as a stratification factor.

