### Experimental arm

After randomization, only patients randomized to the experimental arm will be asked separate informed consent for the immediate analysis of ctDNA status of the post-surgery sample. A small proportion of patients, estimated approximately 5–8% will have detectable ctDNA in their blood. These patients will be offered ACT. Patients decide whether they accept or refuse this treatment. Patients without detectable ctDNA will receive routine standard of care.

ACT will consist of 6 months of capecitabine and oxaliplatin (CAPOX) or 6 months of fluorouracil, leucovorin and oxaliplatin (FOLFOX). Treatment starts preferably within 8 weeks and not beyond 12 weeks after surgery.

During and after completing ACT routine follow-up will consist of regular visits at the surgical outpatient department, blood withdrawals for analysis of carcinoembryonic antigen (CEA) and imaging (standard ultrasound of the liver) according to current guidelines in the Netherlands. No additional imaging will be performed to prevent detection bias.

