#### Quality of life

QoL is measured within the cohort at regular intervals in patients who gave consent to send questionnaires. Nationally and internationally validated questionnaires are used, among which the European Organisation for Research and Treatment of Cancer Quality of Life Questionnaire Core 30 and the ColoRectal cancer module (EORTC-QLQ-C30 and -CR29), the Work Ability Index (WAI), the Euro Quality of life-5 Dimensions (EQ-5D), the Multidimensional Fatigue Inventory-20 (MFI-20) and the Hospital Anxiety and Depression Score (HADS).

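### The quality-of-life model for ctDNA-positive patients includes ACT, a choice made after randomisation, so it does not give the between-arm comparison it announces

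*Protocol article*

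**What the plan says.** All places are in the protocol article.

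- **Data analysis**, on ctDNA-positive patients: "Comparison of QoL of the ctDNA positive patients in both study arms will be done using repeated measurements methods and including ACT as factor". The next sentence extends the QoL analysis to everyone in both arms and does not mention ACT. Then: "Treatment differences at each QoL assessment time point will be compared by means of the Wilcoxon Rank Sum Test".
- **Experimental arm**, on the offer of ACT once ctDNA has been found: "Patients decide whether they accept or refuse this treatment".
- **Sample size considerations**: "We assume that 90% of patients in the intervention arm with detectable ctDNA will be treated with ACT", and "We assume that cross-over from the control arm to the intervention arm will not occur".
- **Quality of life**: "QoL is measured within the cohort at regular intervals in patients who gave consent to send questionnaires".
- **Study design**: the cohort "collects clinical data and Patient Reported Outcome Measures (PROMs) at baseline and at multiple time points during follow-up". Under **Patient selection and recruitment**, patients "will be included in the observational PLCRC substudy MEDOCC (Molecular Early Detection of Colon Cancer) before surgery", whereas randomisation follows about a week after surgery.
- **Analysis principle**: the abstract gives intention to treat without restriction. Data analysis names it only for the primary endpoint and for 2-year recurrence in ctDNA-positive patients.

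**The concern.** The sentence sets out to compare the arms and then puts into the model a variable that arm itself largely determines. ACT is not a baseline characteristic. It follows allocation, the test result and the patient's decision, and any toxicity of the strategy acts through it.

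The wording allows two models. With ACT beside arm, the arm term is what remains after the chemotherapy effect has been taken out. With ACT in place of arm, patients are grouped by what they received. The second model also mixes two states of knowledge: refusers know their ctDNA result and controls do not. The Background section itself describes that knowledge, without treatment on offer, as a heavy burden, and an anxiety and depression scale is among the instruments.

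At stake is what the trial can say about the QoL cost of ctDNA-guided treatment in the patients who are offered chemotherapy. A small, non-significant arm coefficient from the first model could be reported as no difference between arms when it only reflects where the chemotherapy effect was placed.

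**Working it through.** **Plan's own figure.** The QoL analysis has no sample size of its own; its set is the ctDNA-positive patients. The plan's 30 per arm leads to its total: 30 × 1.10 = 33; 33 / 0.05 = 660 per arm; 2 × 660 = 1320. Only patients who consented to questionnaires contribute, so 30 per arm is used here as a favourable case.

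**Inputs.** 30 per arm; ACT in 90% of the intervention arm (27 of 30); ACT in 0 of 30 controls (no cross-over, and eligibility requires no indication for ACT). Simplifications: one visit, ACT coded received or not, main effects only, outcome in SD units.

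**Reading 1: ACT beside arm.**
- Arm and ACT agree in 27 + 30 = 57 of 60 patients (95%).
- phi = (27 × 30 − 3 × 0) / √(30 × 30 × 27 × 33) = 810 / 895.5 = 0.905.
- Variance inflation = 1 / (1 − 0.905²) = 5.5; √5.5 = 2.35.
- SE of the arm effect, arm only: √(1/30 + 1/30) = 0.258 SD.
- SE of the arm effect with ACT added: √(1/3 + 1/30) = 0.606 SD. With no treated controls, the coefficient is simply the mean of 3 refusers minus the mean of 30 controls.
- Detectable difference (80% power, two-sided 0.05, multiplier 2.80): 0.72 SD with arm only, 1.70 SD with ACT added.

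Other uptakes, 30 per arm:

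| Uptake | Refusers | phi | Variance inflation | SE of arm effect (SD) |
|---|---|---|---|---|
| 80% | 6 | 0.82 | 3.0 | 0.447 |
| 90% | 3 | 0.90 | 5.5 | 0.606 |
| 28 of 30 | 2 | 0.94 | 8.0 | 0.730 |
| 100% | 0 | 1.00 | – | not estimable |

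The main loss is in what is estimated, not only in precision. In 20,000 simulated trials with ACT assumed to lower QoL by 0.73 SD, the arm-only model gave −0.65 SD (expected 0.9 × −0.73 = −0.66) and rejected in 69%. With ACT added, the arm coefficient averaged 0.00 and rejected in 5%. When refusers were also assumed to score 0.5 SD lower for their own reasons, the arm coefficient with ACT became −0.50 SD. It follows the refusers, not the strategy.

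**Reading 2: ACT in place of arm.** The 27 treated patients are compared with 33 untreated: 30 controls and 3 refusers.
- Refusal unrelated to QoL: as-treated −0.73 SD against −0.66 SD by arm, a gap of 0.1 × 0.73 = 0.07 SD. At 80% uptake the gap is 0.2 × 0.73 = 0.15 SD.
- Refusers 0.5 SD lower: as-treated −0.73 + (3/33) × 0.5 = −0.68 SD; by arm −0.66 − 0.1 × 0.5 = −0.71 SD.

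The numerical shift is small at the planned uptake, but the contrast is no longer protected by randomisation.

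**Baseline score (secondary).** Adjustment leaves a fraction 1 − ρ² of the variance. The correlation ρ is not in the document; for assumed values of 0.3, 0.5 and 0.7 the remaining variance is 0.91, 0.75 and 0.51, a reduction of 9%, 25% and 49%. The arm-only detectable difference falls from 0.72 to 0.69, 0.63 and 0.52 SD.

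**The case against.** The best reply is that the phrase is ambiguous and the damage bounded. The variance inflation belongs to reading 1 only. Under reading 2 there is no collinearity, and at 90% uptake the estimate moves by less than 0.1 SD in the cases worked above. Under reading 1 the ACT coefficient is itself reported. The whole-population analysis in the same paragraph does not mention ACT, and the rank sum tests, if treatment there means arm, carry no ACT adjustment. All of this stands and limits the size of the point. It does not remove it: under neither reading is the named model a comparison of the randomised arms. Nor could about 3 self-selected refusers support an attempt to separate the effect of knowing the result from that of chemotherapy.

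Three stronger conclusions are tempting, and the document does not support them.

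- *That chemotherapy toxicity would be hidden altogether.* It would leave the arm term but show in the ACT term.
- *That the visit-by-visit tests are faulty because they ignore baseline.* The text does not say whether raw or change scores are ranked, or whether the repeated-measures model includes baseline; an unseen analysis plan may settle both. An unadjusted rank test of randomised arms is valid, only less efficient.
- *That testing six questionnaires at every visit makes a false positive likely.* The article gives neither the number of visits nor the number of scores tested, the tests are correlated, and no confirmatory QoL claim is made. No error rate can be derived.

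**Conclusion.** The point holds in a limited form. The model named for ctDNA-positive patients does not deliver the between-arm QoL comparison that its own sentence announces, and it does not fit the abstract's unrestricted intention-to-treat statement.

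With ACT beside arm, the arm effect rests on about 3 patients against 30, with an SE about 2.3 times larger, and it is not the effect of the strategy. With ACT in place of arm, the result is as-treated; the numerical shift is probably small, but randomisation no longer supports it. These sizes rest on the plan's assumptions of 90% uptake and no cross-over and on 30 respondents per arm. The 0.73 SD effect and the 0.5 SD shift in refusers are illustrative assumptions.

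One secondary endpoint in one subset is affected. The primary endpoint and 2-year recurrence are untouched, and nothing here faults the whole-population QoL analysis as described. The baseline score is a matter of efficiency, not of validity.

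**What to change.** In Data analysis, specify the repeated-measures model for ctDNA-positive patients with randomised arm, visit and arm-by-visit, and remove ACT as a covariate. If the effect of actually receiving ACT is of interest, put it in a separate analysis labelled as non-randomised, and say that its untreated group contains both patients who know their ctDNA result and patients who do not.

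As an optional gain in precision, add the baseline score already collected in the cohort and report arm differences with confidence intervals per visit from this model. If the rank sum tests are kept, state that treatment means randomised arm.

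The cost is a change of wording in the protocol or analysis plan, best made before QoL data are compared by arm. No new data, visits or patients are needed.
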